### Participant timeline

Figure 2 depicts the participant flow for the ISF Experiment, which was organized by the four-phased EPIS framework [29]. For each of the three ASO cohorts, which were spaced 1 year apart, the exploration phase was initiated via the dissemination of standardized project introductions via emails and phone calls to all ASOs within the cohort’s geographically based catchment area (i.e., Central, Western, and Eastern states). ASOs interested in learning more about the project were invited to participate in an introductory meeting (see Recruitment below). Following the meeting, ASOs that met project eligibility criteria were emailed a project participation agreement to be completed and returned to the project’s Principal Investigator for finalizing. Once a cohort’s target number of participation agreements was reached, the exploration phase concluded by having each ASO’s designated SWOP team members (2–4 leadership staff and 2 BI staff) complete a confidential baseline assessment survey. As described in in the allocation section, data from these surveys, conducted under the auspices of RTI’s Institutional Review Board (IRB) and requiring written consent, were used as part of the condition assignment process. Following the completion of the exploration phase, ASOs and their SWOP team completed the project’s three 6-month phases: preparation (months 1–6), implementation (months 7–12), and sustainment (months 13–18).

**Fig. 2 Fig2:**
[figure not shown]
Flow of participating AIDS service organizations (ASOs) *Note*: *t* time; *ATTC* Addiction Technology Transfer Center; *ISF* implementation and sustainment facilitation

#### Sample size

Sample size for the ISF Experiment was determined via power analyses with Optimal Design Software [88]. We assumed an equal number of BI staff (2 per ASO) and an intraclass correlation coefficient of .05. With 78 BI staff nested within 39 ASOs, there is 80% power to detect statistically significant (p < .05) differences when the effect size is .67 or greater.

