### The ISF Experiment’s Objective and Scientific Hypotheses

Testing the effectiveness of the ISF strategy as an adjunct to the ATTC strategy is the ISF Experiment’s key objective. Table 1 lists the planned scientific hypotheses for the ISF Experiment, which were guided by use of a decomposed-first strategy [39] that advocates for starting with moderation-focused hypotheses to avoid biases associated with conflated effects.

**Table 1 Tab1:** Planned scientific hypotheses

Hypotheses	
H1	The positive relationship between the implementation and sustainment facilitation and staff time-to-proficiency will be moderated by
	H1a Staff’s motivational interviewing experience
	H1b Staff’s personal recovery status
	H1c Organization’s readiness for implementing change
	H1d Organization’s implementation climate
	H1e Organization’s leadership engagement
	H1f Organization’s tension for change
H2	The positive relationship between the implementation and sustainment facilitation and staff implementation effectiveness will be moderated by
	H2a Staff’s motivational interviewing experience
	H2b Staff’s personal recovery status
	H2c Organization’s readiness for implementing change
	H2d Organization’s implementation climate
	H2e Organization’s leadership engagement
	H2f Organization’s tension for change
H3	The positive relationship between the implementation and sustainment facilitation and staff level of sustainment will be moderated by
	H3a Staff’s motivational interviewing experience
	H3b Staff’s personal recovery status
	H3c Organization’s readiness for implementing change
	H3d Organization’s implementation climate
	H3e Organization’s leadership engagement
	H3f Organization’s tension for change
H4	Staff implementation effectiveness will mediate the relationship between staff time-to-proficiency and staff level of sustainment

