### Statistical methods

Statistical analyses will be conducted using an intention-to-treat analysis approach, which will analyze all ASOs as randomized. Hot-deck imputation [95, 96] will be used to address missing data issues, which are anticipated to be minimal (i.e., less than 5%). Analyses will be conducted using HLM software [97], which is well-suited for handling clustered data (i.e., time nested within staff, nested within organization). Analyses will be conducted in the order outlined in Table 1. In addition to reporting the coefficient, standard error, 95% confidence interval, and *p* value, results will also include effect size indicators.

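### The stated power (.67 at 80%) belongs to an ISF main-effect test that Table 1 does not list; it does not describe the 18 moderation tests that Table 1 does list

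*Protocol article*

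**What the plan says.** Protocol article, The ISF Experiment's Objective and Scientific Hypotheses: the key objective is "Testing the effectiveness of the ISF strategy as an adjunct to the ATTC strategy". Table 1 in that section gives the planned hypotheses. H1 to H3 share one form, for example H2: "The positive relationship between the implementation and sustainment facilitation and staff implementation effectiveness will be moderated by". Each is followed by the same six moderators (a to f), two at staff level and four at organization level. H4 is a mediation hypothesis that links the three outcomes and does not involve condition.

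Statistical methods: "Analyses will be conducted in the order outlined in Table 1".

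Sample size: "We assumed an equal number of BI staff (2 per ASO) and an intraclass correlation coefficient of .05". For the planned 39 organizations and 78 staff, the section then concludes that "there is 80% power to detect statistically significant (p < .05) differences when the effect size is .67 or greater". The test behind this figure is not named, and no other power figure is given.

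**The concern.** The objective, the list of hypotheses and the power basis do not fit together. The objective asks about the overall effect of ISF. The list presumes that effect and asks only what modifies it. The power figure is then given for unspecified differences, so a reader will naturally attach it to the hypotheses in Table 1.

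Two things are at stake. First, an analyst who followed Table 1 and its order literally would run no listed test of the average ISF effect, and one who added it would go beyond the published hypotheses. Either way, the trial's main claim would lack a clear prespecified test. Second, 80% power at .67 could be read as covering the moderation tests. A non-significant moderator might then be taken as evidence that no sizeable moderation exists, which a trial of this size cannot show.

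**Working it through.** **Inputs.** From Sample size: J = 39 ASOs, m = 2 BI staff per ASO, ICC = .05, significance level .05, power 80%, detectable effect .67. Neither the allocation ratio nor the sidedness is stated. I assume 1:1 (a 19:20 split gives the same answer to two decimals) and two-sided testing, because only two-sided testing reproduces .67.

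**1. The plan's own figure (main effect of condition, one outcome).**
- SE = sqrt[4 × (ICC + (1 − ICC)/m) / J] = sqrt[4 × (.05 + .475)/39] = sqrt(.05385) = .232.
- Degrees of freedom: 39 − 2 = 37.
- Noncentral t, two-sided .05: detectable effect at 80% power = 2.877 × .232 = .668. Power at .67 is 80.3%.
- A one-sided test would give .588, which does not match.

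So .67 is right, and it is the detectable main effect of condition.

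**2. What Table 1 lists.** 3 outcomes × 6 moderators = 18 condition-by-moderator hypotheses, plus H4. None is the comparison in step 1.

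**3. Same inputs, balanced binary organization-level moderator (assumed 50/50 split).** The interaction is a difference of two differences, each from half the ASOs.
- SE = 2 × .232 = .464, with 39 − 4 = 35 df.
- Detectable difference in ISF effect = 2.881 × .464 = 1.34 SD.
- Power if the ISF effect differs by .67 between the halves: 29%.

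**4. Same inputs, continuous organization-level moderator, standardized.**
- SE per SD of moderator = .232, with 35 df.
- Detectable change in ISF effect = .67 SD per SD of moderator, or 2 × .67 = 1.34 between −1 and +1 SD.
- If the effect changes by .67 over that span (.335 per SD), power is again 29%.

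**5. Same inputs, binary staff-level moderator such as recovery status (prevalence not given, so assumed).** The detectable difference is about 1.30 SD at 50% prevalence, 1.42 at 30% and 1.64 at 20%. Power at .67 is about 30%, 26% and 21%.

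**6. Main effects under a Holm procedure, if one is chosen.** The first step for three outcomes uses .05/3 = .0167. The detectable effect is 3.367 × .232 = .78.

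**7. Conditional point on multiplicity.** If each of the 18 tests were read at an unadjusted .05:
- Under independence, familywise error is 1 − .95^18 = 60%.
- With assumed correlations of .5 to .7 among moderators and .3 to .5 among outcomes, simulation gives about 47 to 54% if the two staff-level moderators are independent of the rest, and about 37 to 48% if all six are correlated.
- With all correlations at .7 and all six moderators correlated, it is about 33%.

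**The case against.** The strongest reply is that the main effect is stated throughout, apart from Table 1. The abstract says effectiveness is examined through three staff-level measures, and the Outcomes section repeats this. The Fig. 1 legend distinguishes hypothesized relationships from interactions to be examined. The decomposed-first rationale describes moderation as where one starts, which implies later steps. This stands. A reader might infer that the trial has no test of its own question, or that the average effect will never be estimated; the documents do not support that. The defect is that the intended test is not listed where the plan lists its tests.

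The Sample size section also makes no explicit claim about interactions, and for a continuous moderator the detectable value is numerically .67 as well. Both points are fair. But .67 per SD of moderator is a different quantity from a .67 difference between arms, and the section does not say which test it means.

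Three further inferences should not be drawn:
- **The condition coefficient in a moderated model is the effect at moderator zero, for example staff with no MI experience.** That assumes uncentred moderators. Coding is not stated and is ordinary analysis-plan content.
- **All 18 tests will be read at .05 without adjustment.** The only .05 threshold is in the power sentence. Statistical methods promises estimates, intervals and p values without a decision rule, and a multiplicity rule may sit in an analysis plan not shown.
- **A false moderator finding is more likely than not.** That needs unadjusted testing and near-independence. Four of the moderators are organizational averages from the same staff surveys, so correlation is plausible.

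**Conclusion.** The point holds as a mismatch between objective, listed hypotheses and power basis. The .67 is arithmetically correct (.668, 37 df), but it belongs to an unmoderated comparison on a single outcome at two-sided, unadjusted .05, and Table 1 does not contain that comparison. The moderation tests it does contain have 80% power only for large interactions: about 1.34 SD between equal halves, or .67 SD per SD of a continuous organization-level moderator. For a .67 difference between equal halves, power is about 29%.

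These interaction figures use the plan's own J, m and ICC, with assumed 1:1 allocation and assumed moderator distributions. The multiplicity figures (60% under independence, roughly 35 to 55% under plausible correlation) are conditional on unadjusted testing, and the finding does not depend on them.

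This should be corrected: as written, the trial's central comparison is missing from its own list of planned tests. The correction needs wording only, with no new data.

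**What to change.** - **Table 1:** add three directional main-effect hypotheses: ISF leads to fewer days to proficiency, higher implementation effectiveness, and higher sustainment at the month-19 survey. State that each is estimated from a model without interactions. Spelling out the direction also removes an ambiguity in H1, where a positive relationship with a count of days would literally mean slower proficiency.
- **Sample size:** state that .67 applies to each of these main effects at two-sided, unadjusted .05. If Holm is used across the three outcomes, add that the first-step figure is about .78. Whether to use Holm is the investigators' choice.
- **Moderation hypotheses:** either give the detectable interaction sizes with the assumed moderator distributions, or label H1a to H3f secondary or exploratory. If they stay confirmatory, say how error over the 18 tests is handled, or refer to the analysis plan that says so.

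**Cost:** a less favourable power statement and, if that option is taken, loss of confirmatory status for the moderators. Table 8 shows cohort 1 through sustainment and cohort 2 through implementation, so this is a change during the trial. It needs a dated, documented amendment that says whether outcome data by condition had been seen.

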#### Recruitment

The identification and recruitment of ASOs was conducted by the Principal Investigator (BG) and project coordinators (DK, EB). Potential ASOs were identified via searches of organization directories [89, 90]. Identified ASOs were sent standardized introduction emails, with follow-up calls completed as necessary by project coordinators. ASOs interested in learning more about the project participated in a 45- to 60-min, organization-specific, Web-assisted, informational webinar, which was conducted by the Principal Investigator or one of the project coordinators.

In addition to providing information about the project, a key goal of the informational webinar was to gather information about the ASO, including (a) whether describing their organization as a community-based ASO was accurate, (b) the key services provided to individuals living with HIV/AIDS, (c) the number of individuals living with HIV/AIDS served annually, (d) the number of case-management staff, (e) their level of interest in participating in the project, and (f) their reasons for wanting to participate. Upon review of the collected information, the Principal Investigator and project coordinators identified ASOs that did not represent a good fit for the project. ASOs deemed to be a good fit were contacted via email and/or phone, and official participation was documented by having the ASO’s signing official sign and date a project participation agreement.

### Assignment of interventions

#### Allocation

Participating ASOs were assigned to one of two study conditions via urn randomization [91]. Using staff survey data collected during the exploration phase from the BI staff and leadership staff, seven organizational-level factors (importance of substance use screening, importance of brief intervention for substance use, innovation-value fit, implementation strategy-value fit, implementation climate for substance use brief intervention, implementation readiness for substance use brief intervention, and implementation effectiveness for substance use brief intervention) were entered into the urn randomization program gRAND [92], which optimized the balance of the two study conditions on these seven factors. Written consent was obtained from BI staff and leadership staff before survey completion.

#### Blinding (masking)

ASOs and their staff were not blinded to study condition. However, the ATTC training and rating staff were blinded to study condition.

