*F. Conduct educational meetings*: Hold meetings targeted toward providers, administrators, other organizational stakeholders, and community, patient or consumer, and family stakeholders to teach them about the clinical innovation	Regional ATTC	In-person and Web-based meetings that enable direct interaction between the actors (ATTC) and targeted users of the EBP (BI staff)	2 BI staff per ASO	Educational meetings should begin at least 3 months before the implementation phase begins	See Tables 4, 5 and 6	Fidelity (i.e., proficiency and implementation effectiveness)	[30, 36, 55, 61]
*G. Make training dynamic*: Vary the information delivery methods to cater to different learning styles and work contexts and shape the training in the innovation to be interactive	Regional ATTC	Incorporate standardized role plays that enable EBP trainees (BI staff) to practice with each other and that facilitate understanding of the EBP from both staff and client perspectives	2 BI staff per ASO	Should begin during the first contact	See Tables 4, 5 and 6	Fidelity (i.e., proficiency and implementation effectiveness)	[55, 56, 101, 102]
*H. Audit and provide feedback*: Collect and summarize clinical performance data over a specified period, and give data to clinicians and administrators in the hopes of changing provider behavior.	Regional ATTC	Generate and email standardized feedback reports to EBP trainees (BI staff) using the standardized quality monitoring tool (ITRS)	2 BI staff per ASO	Should begin approximately 1–2 weeks following the end of the in-person educational training workshop	See Tables 4, 5 and 6	Fidelity (i.e., proficiency and implementation effectiveness)	[30, 57–60]
*I. Provide ongoing consultation*: Provide clinicians with continued consultation with an expert in the clinical innovation	Regional ATTC	Phone-based individualized meetings that enable direct contact between the actor (ATTC trainer) and one EBP trainee (BI staff)	2 BI staff per ASO	Should begin approximately 1–2 weeks following the end of the in-person educational training workshop	See Tables 4, 5 and 6	Fidelity (i.e., proficiency and implementation effectiveness)	[30, 36, 61]

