*J. Create a learning collaborative*: Develop and use groups of providers or provider organizations that will implement the clinical innovation and develop ways to learn from one another to foster better implementation	Regional ATTC	Web-based group meetings that enable direct contact between the actor (ATTC trainer) and a group (10–14 targeted users of the EBP, BI staff), who can share lessons learned	2 BI staff per ASO	Should begin approximately 3–4 weeks after the implementation phase begins	See Tables 4, 5 and 6	Fidelity (i.e., proficiency and implementation effectiveness)	[63–65]

**Table 3 Tab3:** Specification overview of the multifaceted implementation and sustainment facilitation (ISF) Strategy

Discrete implementation strategies: Defining characteristic according to Proctor et al. [41]	Operational definition of key dimensions for each discrete implementation strategy						
	Actor(s)	Actions(s)	Target(s) of the action	Temporality	Dose	Targeted implementation outcome(s)	Justification
*K. Use an improvement and implementation advisor*: Seek guidance from experts in implementation, including consultation with outside experts (e.g., university-affiliated faculty members, quality improvement experts, implementation professionals)	An individual with training and experience in assisting organizations with practice improvement and implementation efforts	The overarching implementation strategy that encompasses the other discrete implementation strategies listed below	An ASO’s designated staff working on the project (SWOP) team (2 BI staff and 2–4 leadership staff) Implementation readiness, implementation climate, leadership engagement	The initial kickoff meeting should be held within 1 month of completing the exploration phase	See Tables 4, 5 and 6	Fidelity (i.e., proficiency and implementation effectiveness) and sustainment	[38, 66–69]

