Distribute educational materials Consistent with research supporting the importance of using multiple dissemination strategies [45, 46, 54], the educational materials were distributed to BI staff. BI staff were emailed links to the online educational course [47] and printed copies of the MIBI protocol manual [48] were hand-delivered to staff at the in-person workshop training.(F)
Conduct educational meetings Research has not found educational materials by themselves to be sufficient for learning motivational interviewing [30, 55]. Thus, Web-based and in-person educational meetings were also provided, including a two-day in-person workshop training for BI staff on the MIBI protocol.(G)
Make training dynamic Role plays that enable trainees to practice with other trainees and facilitate understanding of the EBP from both the staff and client perspectives have been found to make motivational interviewing training more dynamic [30, 55, 56]. In addition to using role plays multiple times during the in-person workshop training, trainees were given role plays to complete during the week after the workshop training.(H)
Audit and provide feedback There is support for audit and feedback as an effective strategy, both in general [57–60] and specifically with learning motivational interviewing [30]. Thus, standardized feedback reports based on ratings using the validated Independent Tape Rater Scale [26] were provided to BI staff for all sessions completed and recorded.(I)
Provide ongoing consultation Providing ongoing consultation following workshop training has been supported as an important strategy to facilitate learning of psychosocial interventions [30, 36, 61]. During the 10-week post-workshop-training practice period, each trainee was allowed up to four individual consultation sessions with a member of the Motivational Interviewing Network of Trainers (MINT) [62].(J)
Create a learning collaborative The use of a learning collaborative has been identified as an important method of learning [63–65]. Thus, each month during the 6-month implementation phase, a motivational interviewing expert from MINT [62] organized and moderated two 1-h learning collaborative meetings, one for the ATTC only condition and one for the ATTC plus ISF condition.

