Staff survey	X^c^			X^c^	X^c^	Readiness for implementing change (moderator variable) A continuous organization measure (ranges from 1 to 5) that represents the organizational average of 6 items, each rated on a 5-point scale (1 = disagree, 2 = somewhat disagree, 3 = neither agree nor disagree, 4 = somewhat agree, 5 = agree) and adapted from Shea et al.’ readiness measure [106]
Staff survey	X^c^			X^c^	X^c^	Implementation climate (moderator variable) A continuous organization measure (ranges from 1 to 5) that represents the organizational average of 6 items, each rated on a 5-point scale (1 = disagree, 2 = somewhat disagree, 3 = neither agree nor disagree, 4 = somewhat agree, 5 = agree) and adapted from Jacobs et al.’ implementation measure [107]
Staff survey	X^c^			X^c^	X^c^	Leadership engagement (moderator variable) A continuous organization measure (ranges from 0 to 6) that represents the organizational average of 4 items, each rated on a 7-point scale (0 = not at all to 6 = highest extent possible) and developed for this study based on the leadership engagement construct described by Damschroder et al.—commitment, involvement, and accountability of leaders with the implementation [108]
Staff Survey	X^c^			X^c^	X^c^	Tension for change (moderator variable) A continuous organization measure (ranges from 0 to 6) that represents the organizational average of 3 items, each rated on a 7-point scale (0 = not at all to 6 = highest extent possible) and developed for this study based on the tension for change construct described by Damscroder et al.—stakeholders’ shared perception of the extent to which a change is important, needed, and desired [108]

^a^Ratings during the preparation phase were completed by one of the co-authors (DV)

^b^Ratings during the implementation phase were rated by one of 15 experienced raters, each of which were trained, calibrated, and monitored by one of the co-authors (SM)

^c^Staff surveys (electronically administered) required approximately 30 min to complete, and staff received one $25 e-gift card per completed survey as compensation

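### The masking section says without qualification that ATTC training staff were blinded, but an ATTC trainer organized and ran separate monthly meetings for each condition in the implementation phase

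*Protocol article*

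**What the plan says.** The section Blinding (masking) has two sentences. The first says that "ASOs and their staff were not blinded to study condition". The second says: "However, the ATTC training and rating staff were blinded to study condition". The second is not limited by phase, task or person.

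Under Addiction Technology Transfer Center strategy, item (J), the learning collaborative is described as follows: "each month during the 6-month implementation phase, a motivational interviewing expert from MINT" "organized and moderated two 1-h learning collaborative meetings, one for the ATTC only condition and one for the ATTC plus ISF condition".

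Table 2, row J, lists the Regional ATTC as actor for this strategy and describes "Web-based group meetings that enable direct contact between the actor (ATTC trainer) and a group" of BI staff, who exchange what they have learned. It places the start about 3 to 4 weeks into the implementation phase.

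Rater masking is stated twice: in the Blinding section, and again under Data collection and management for the 15 raters of recorded sessions.

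**The concern.** ISF is tested as an adjunct to ATTC, so both arms receive ATTC and the comparison assumes that it is delivered alike in both. Blinding the ATTC trainers would protect that assumption, because a trainer who does not know the arm cannot adjust effort to it. Someone who convenes one group per condition each month and talks with attendees who know their assignment is hard to describe as blinded.

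If the moderator knew the arm, encouragement or coaching could differ between groups and its effect would be read as an effect of ISF. Blinded rating does not close this route. Table 7 builds implementation effectiveness from two parts: the number of brief interventions delivered and the integrity of delivery. Encouragement can raise the count without any rating being involved, and better coaching can raise true quality, which a blinded rater would record correctly. If the statement is carried into the results paper, readers will credit the trial with a protection that its design does not give for this role.

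**Working it through.** No formula governs this point, and the masking statement enters no sample-size or power figure. The check sets the passages side by side.

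1. **Is the moderator one of the ATTC training staff?** Item (J) calls the moderator a motivational interviewing expert from MINT. Table 2, row J, calls the actor the ATTC trainer, under the Regional ATTC. The same pairing occurs for individual consultation: Table 2, row I, has "Phone-based individualized meetings that enable direct contact between the actor (ATTC trainer) and one EBP trainee (BI staff"), while item (I) in the text says the sessions were with a MINT member. The article therefore uses the two labels for one role, and the moderator falls within the masking sentence.

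2. **Were the meetings formed by condition?** Item (J) says so directly. The head count agrees. Inputs: 78 BI staff (Sample size), 3 cohorts (Participant timeline), 2 conditions. Assuming equal cohorts and 1:1 allocation, 78 / 3 / 2 = 13 BI staff per condition per cohort. Whole organizations contribute 2 staff each, so 6 or 7 organizations give 12 or 14. Table 2, row J, gives groups of 10–14.

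3. **Could the moderator have remained masked?** Attendees knew their condition and were in direct contact with the moderator. In the ISF arm they also had a monthly advisor meeting in this phase (Table 5) and typically one in-person meeting in its second month (item M). The article describes no masked group labels and no instruction to attendees not to reveal their condition.

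4. **Which outcomes fall in the window?** The meetings run within months 7–12.
   - Time-to-proficiency is assessed in months 1–6, so within a cohort it precedes the meetings. Other cohorts consist of different organizations from other catchment areas.
   - Implementation effectiveness is assessed in months 7–12 and coincides with the meetings.
   - Level of sustainment covers months 13–18. ATTC is no longer provided then (note to Table 6), so any influence would be carry-over from the earlier phase.

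5. **Does any passage reconcile the two statements?** None does. The limitations in the Discussion mention the short sustainment period, self-report and the absence of cost-effectiveness, but not masking of trainers.

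**The case against.** The strongest reply is that the article never says the moderator was told which group was which. Item (J) labels the meetings from the authors' side, and a coordinator could have supplied two unlabelled lists. That is correct as far as it goes: the moderator's knowledge is inferred, not stated. But item (J) has the same expert organizing the meetings as well as moderating them, and the attendees were unblinded. An unqualified blinding claim then needs an explanation that the article does not give.

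Separate meetings are also a sensible way to limit contamination between arms, which the Background gives as the reason for the cluster design. This stands. The fault is in the masking statement, not in holding the meetings separately.

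A reader might infer more than the article supports:

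- *That all ATTC trainers were unblinded.* Item (J) concerns the moderator. Nothing shows that those who gave the workshop or the individual consultation knew the condition.
- *That ratings are open to detection bias.* Table 7 notes that "Ratings during the preparation phase were completed by one of the co-authors", who is distinct from the 15 raters. The Blinding section nevertheless covers rating staff without exception, and no passage says that any rater trained or moderated BI staff. Supposing such an overlap would be an argument from silence.
- *That time-to-proficiency is biased.* The order of events in step 4 gives no support for this.

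**Conclusion.** The Blinding section and item (J) cannot both stand as written for the learning-collaborative moderator. The stated protection against differential co-intervention is not delivered by the described design for that role in months 7–12. The outcomes exposed are implementation effectiveness directly and level of sustainment by carry-over.

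The size and direction of any bias cannot be derived from the article. No planned analysis or power figure changes. What changes is the claim that can be made about performance bias.

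The conclusion rests on two readings: that the MINT expert in item (J) is the ATTC trainer of Table 2, which the parallel wording for consultation supports; and that convening groups by condition with unblinded attendees reveals the condition, which is an inference but a strong one. Masking of raters, and of trainers during the preparation phase, is not contradicted.

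**What to change.** Limit the masking statement to the staff who were masked. For example: *ITRS rating staff, and ATTC trainers during the preparation phase, were blinded to condition; learning-collaborative moderators in the implementation phase were not.* The part on trainers in the preparation phase should be kept only if the investigators confirm it. If the moderators were in fact kept masked, say how.

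Add to the limitations that differential delivery of the ATTC strategy (performance bias) is possible for implementation effectiveness and sustainment.

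This costs two sentences and a check with the ATTC staff on who knew what and in which phase. No extra analysis is needed. The downside is a less favourable masking statement.
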